## 16 INSURANCE

Insurance is covered by “Versicherung für klinische Versuche und nichtklinische Versuche“ by Zürich Versicherungs-Gesellschaft AG (Policy no.: 14.970.888).

Any damage developed in relation to study participation is covered by this insurance. So as not to forfeit their insurance cover, the participants themselves must strictly follow the instructions of the study personnel. Participants must not be involved in any other medical treatment without permission of the principal investigator (emergency excluded). Medical emergency treatment must be reported immediately to the investigator. The investigator must also be informed instantly in the event of health problems or other damages during or after the course of study treatment.

The investigator will allow delegates of the insurance company to have access to the source data/documents as necessary to clarify a case of damage related to study participation. All involved parties will keep the patient data strictly confidential.

A copy of the insurance certificate will be kept in the Investigator's Site File.

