Should symptoms of a previously controlled disease worsen after deprescribing, or if the activity of a disease increases in the post hospital course, then there will always be the option to revert the change and to re-introduce the original medication. In order to avoid virtually any pharmacology-related negative consequences of a deprescription, the discharging HP will be sensitized towards this problem (e.g. stepwise reduction of corticosteroids or anticoagulants).

Provided that our systematic approach will successfully prove its effectiveness in avoiding polypharmacy-induced health problems, we expect it to initiate a change in health professionals' and patients' thinking towards prioritizing, patient-centeredness, and refraining from the prescription of too many drugs for polymorbid patients. As a result, we hope to see a decrease in drug-caused health problems, medical complications, hospitalizations and unnecessary deaths, as well as a reduction in the costs entailed.

Our approach may serve as a model for an optimized discharge procedure, and we therefore expect that colleagues may welcome the suggestions in the dissemination phase. However, we also expect that a proportion of patients and caregivers may have difficulties to adopt this new kind of approach, as some barriers towards deprescribing are known from the literature (37, 42, 43, 52).

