## 8 STUDY INTERVENTION

### 8.1 General Information and Administration of Interventions

#### 8.1.1 Study Intervention

The intervention takes place on different levels with different target populations:

- a. *Teaching session (“Teach-the-Teachers”) for the senior HPs in charge of postgraduate training and supervision of the interns (assistant physicians)*

The purpose of this training of two hours duration is to integrate the discharge procedure (see below) into the daily work of the HPs during the study period. Consecutively, the senior HPs will teach the interns how to apply the structured discharge procedure. This will guarantee the consistency of the intervention even if the fluctuation among interns is high due to organized job rotations within hospitals.

The teaching session will address the following items:

- How to identify patients eligible (possibly in collaboration with nurses)
- How to handle the in- and exclusion criteria
- How to apply the medication review tool (discharge checklist in forms 5b and 5c, see list of study instruments in appendix 18.1) which has been previously tested (15, 32) to the medication plan of the patient before discharge by the HP
- How to involve the senior HP responsible for the interns’ supervision in the medication review, depending on the clinic’s/wards’ usual discharge procedures
- How to involve patients in the changes suggested by the HP
- How to create a discharge medication plan for the patient, after the decision is taken
- How to involve the GPs in the post-discharge phase. An offer for the GP to call the HP in order to discuss the medication plan is prepared on the discharge medication plan. This should guarantee a consensus between HP and GP in order to increase the GPs’ adoption of the changes suggested on the long term
- How to deal with the different data collection forms

- b. *The intervention at discharge*

The intern HP performs a critical review of the medication plan, supervised by his senior HP, discusses the results of this review and his suggestions with the patient and creates a discharge medication plan to be used by the patient. The patient is encouraged to consult his GP within seven days.

Furthermore, the intern HP communicates all medication changes (cessation of specific medication, change of dosage, introduction of new drugs) to the patient’s GP in written form, accompanied with an invitation to the GP to discuss any medication changes (forms 5b and 5c, see appendix 18.1).

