## **8.4 Concomitant Interventions**

Patients may receive any drug or other therapy for any illness before and during the study, and no specific rules will prohibit any such treatment. All treatments will be documented in the patients' personal medical records as usual.

Personal, social, professional or economic circumstances that might affect a patient's state of health are captured globally within the QoL-questionnaires.

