### **13.5 Confidentiality, Data Protection**

Direct access to source documents will be permitted to the CEC for purposes of monitoring, audits and inspections, during and after conclusion of the study.

For contact maintenance and case tracking (e.g. in case of adverse events), the patients' identities will be known to a study nurse not involved in the analysis of the patient data. The patient names will not be accessible to the scientific study staff.

All electronic data, including interview transcripts, will be stored under password protection on secure network drives of the UniversityHospital Zurich.

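### Section 16 requires the principal investigator's permission for any other non-emergency treatment, while section 8.4 says no rule prohibits any treatment; the two must be reconciled

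*Protocol*

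**What the plan says.** Protocol section 16 (Insurance) sets conditions for participants. It first says: "So as not to forfeit their insurance cover, the participants themselves must strictly follow the instructions of the study personnel". The next sentence is: "Participants must not be involved in any other medical treatment without permission of the principal investigator (emergency excluded". It then adds: "Medical emergency treatment must be reported immediately to the investigator". Emergency treatment is therefore exempt from permission but has to be reported.

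Protocol section 8.4 (Concomitant Interventions) says: "Patients may receive any drug or other therapy for any illness before and during the study, and no specific rules will prohibit any such treatment".

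Four other sections assume that ordinary care goes on without a permission step:

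- Section 3.6 (Risks and Benefits), on worsening after a drug is stopped: "there will always be the option to revert the change and to re-introduce the original medication".
- Section 2.2 (Categorization of the Study) supports the category A classification partly by the argument that a medication change can be undone at once. The synopsis gives the same reason.
- Section 8.1.1 (Study Intervention): "The patient is encouraged to consult his GP within seven days".
- Section 8.2 (Compliance with Intervention) repeats the encouragement and adds that not going is no violation.

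**The concern.** One document gives two opposite rules on the same matter for the same people. A patient who sees a GP for a routine problem, has a drug restarted or enters hospital electively acts within section 8.4. Read literally, the same patient breaches section 16 unless permission was obtained first.

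Three things are at stake. The first is insurance: it is unclear whether a participant who followed section 8.4 would still be covered for study-related damage. The second is the safety argument: prior permission for non-emergency treatment is hard to square with the prompt reversal on which sections 3.6 and 2.2 rely. The third is the comparator: section 8.1.2 defines control as usual care, and a permission requirement on ordinary treatment, if applied, is not part of usual care.

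**Working it through.** The point is textual. It depends on no rate, effect size, alpha or power, and the plan gives no figure to reproduce. The check is whether the two rules can be read so that both hold.

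1. **Same people?** Section 16 speaks of participants and section 8.4 of patients. Neither limits its rule to one arm or to a subgroup. Both therefore apply to all 2,100 patients planned in section 11.2.

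2. **Same period?** Section 8.4 covers the time before and during the study. Section 16 gives no time limit for its treatment rule. They overlap at least for the 6 months of follow-up.

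3. **Same treatments?** Section 8.4 covers any drug or therapy for any illness. Section 16 covers any other medical treatment except emergencies. Nothing in the protocol narrows section 16 to experimental or study-related treatment. Section 7.4 describes the intervention as given once and not continued, so on the literal wording nearly all care after discharge is other treatment. The overlap is all non-emergency care.

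4. **Can both hold?** Section 8.4 says that no rule prohibits such treatment. Section 16 is a rule that prohibits it unless permission is given. Within the overlap they cannot both be true.

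5. **How often would the overlap arise?** Section 7.1.1 admits patients aged 60 or older on five or more drugs, so some non-emergency care within 6 months is to be expected for most of them. The document gives no frequency, and none is assumed here.

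6. **Which recorded outcomes lie in the overlap?** Section 5.1 counts any readmission within 6 months without separating elective from emergency admissions; only the elective ones fall under the permission rule. Section 5.2 counts GP encounters. It also records number of drugs, ATC codes and potentially inappropriate medications at 1, 3 and 6 months. Reversal of a drug change is not a named outcome but would show in those drug measures. Emergency readmissions and emergency ED visits lie outside the overlap.

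7. **Is a permission step described anywhere else?** Sections 9.3.1 to 9.3.7 list the procedures at each stage and contain none. The instruments in appendix 18.1 include no permission form.

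**The case against.** The strongest reply is that section 16 is administrative insurance wording and section 8.4 is the operative rule. No permission step appears in the procedures. Section 7.4 says that discontinuing a participant for not adhering to protocol requirements is not possible. The cover concerns damage related to study participation, not access to ordinary care. It can also be said that the GP visit in section 8.1.1 is prompted by study staff, so attending it follows their instructions and is arguably not other treatment. Much of this is fair. It makes it likely that section 8.4 reflects what was intended, and it weakens section 8.1.1 as a contradiction in its own right. It does not narrow the words of section 16, and it does not settle whether cover is kept by a patient whose treatment is changed at such a visit.

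A reader might also infer more than the document supports:

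- *That patients are told opposite things.* Patient letter 3d is not shown, so what patients are told is unknown. Only the protocol's own sections can be seen to conflict.
- *That the rule obstructs readmissions in general.* Emergencies are exempt, and the document gives no share of elective admissions.
- *That the rule cannot be operated.* Section 13.5 does say: "The patient names will not be accessible to the scientific study staff". The same paragraph, however, provides a study nurse who knows patients' identities for contact and case tracking, so a route could exist. Nor does the protocol as available say whether the principal investigator treats any of the patients.
- *That events are suppressed, power is lost or the arm comparison is biased.* Nothing shows that patients or GPs would act differently because of section 16.

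**Conclusion.** The contradiction stands as written. For non-emergency care, sections 16 and 8.4 cannot both apply, and no other section resolves the conflict. It covers every planned participant through follow-up. Its demonstrable consequences are uncertainty about insurance cover, and a poor fit with the reversibility argument in sections 3.6 and 2.2 and with usual care in section 8.1.2. Any effect on the primary or secondary outcomes cannot be derived from the document, so no claim about power or bias is made.

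The conclusion rests on reading section 16 literally and on its treatment rule being a condition of cover. The second is an inference from its place directly after the sentence on forfeiture. If the insurer confirms a narrower meaning, the conflict becomes one of wording only, but the text would still need correcting.

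**What to change.** Reconcile section 16 with sections 8.4, 3.6, 2.2, 8.1.1 and 8.2 so that one rule on other medical treatment applies throughout. Confirm that rule with the insurer, and check patient letter 3d against it. The sponsor and the insurer decide which rule stands.

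If a permission step is kept, section 8.4 and the study procedures must state it and say how it is operated, for example through the study nurse who knows patients' identities. Sections 3.6 and 2.2 must then be made consistent with it.

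The cost is protocol wording, patient-letter wording if the check shows a need, and one confirmation from the insurer. Sample size, outcomes and analysis do not change.

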## 18 APPENDICES

### 18.1 List of Study Instruments

- 3a: Information letter for senior HPs
- 3b: Informed consent form for senior HPs  
incl. hospital and clinic descriptors (type and size in terms of number of beds)
- 3c: Information letter for intern HPs
- 3d: Information letter for patients
- 3e: Informed consent form for patients  
incl. patient characteristics (age, sex)
- 5a: CRF at discharge («study tool»)  
version 1 with medication changes, discharge checklist and communication offer for GP
- 5b: CRF at discharge («study tool»)  
version 2 with discharge checklist and communication offer for GP
- 5c: Quality of life questionnaire (at discharge)
- 5d: CRF at 1, 3 and 6 months after discharge (identical)  
incl. readmissions, ED visits and GP encounters with reasons,  
and incl. quality of life questionnaire
- 5e: Record form for frequency of GP-HP communication  
and feasibility & acceptance questionnaire for HPs (5 point likert scale)
- 5f: Interview guide to assess barriers & enablers
- 11a: Checklist with in- and exclusion criteria for recruiters
- 11b: Participant list (list of included patients)
